### Sample Size of the Quantitative Surveys

The sample size of RDW to be included in the baseline and end line surveys was determined to generate indicators for each of the 3 HRP conditions (moderate or severe anemia, PIH, and APH) separately for the intervention and usual care arms. To achieve this, the sample size was estimated based on the HRP condition, with the lowest prevalence among the 3 conditions. This approach ensures that the sample size estimated for an HRP condition with the lowest prevalence will suffice for the HRP conditions with higher prevalence as well, using the most recent prevalence data for the HRP conditions among the pregnant women in India or North India.

From recent available literature in India, the prevalence of moderate or severe anemia among pregnant women in the north zone was 25% [39], PIH in India ranged from 5%‐17% [40], and prevalence of only APH is 2%‐5%, and placenta previa is 4%‐5% [41]. It implies, among the 3 HRP conditions, PIH has the lowest prevalence. Assuming the prevalence of PIH among RDW in the intervention arm and in the control arm, at baseline and end line surveys is 5%, the estimated sample size for PIH is not expected to differ by more or less than 1% (ie, 4%‐6% is the margin of error), with a 95% confidence level, the sample size of RDW required in both the intervention and in usual care arms, at baseline and at end line surveys is 1825 (rounded to 2000) [42]. It means we need to interview 2000 RDW in each arm, both at baseline and end line surveys to generate required sample size for each HRP condition. Assuming the above prevalence of HRPs holds true in the 2 study arms, by interviewing 2000 RDW cross-sectionally in each arm, we anticipate at least 400‐500 RDW with moderate or severe anemia, 120‐200 RDW with APH, placenta previa, or abruptio placenta, and 100‐340 women with PIH. Some of these RDW may have more than 1 of the 3 HRP conditions. Approximately 900‐1000 RDW in each arm will be without any of the 3 HRP conditions.

Given the low prevalence of PIH and APH (around 5%), with 1% margin of error, our study (2000 RDW per arm) is adequately powered at 95% (a conservative estimate). With a higher margin of error (say 1.5%), although the required sample size per arm will reduce to 821, the power of the study will fall below 95%, and the anticipated number of RDW with PIH and APH would be too small to compare (approximately 70‐130 per arm). This would result in high CIs, making HRP-specific impact evaluation a challenging task.

As different respondents will be surveyed at baseline and end line, there is no risk of data attrition. However, since HRP conditions data in this study is relying on self-reports by RDW and expected low prevalence of PIH and APH conditions (around 5%) in India, nonparticipation by RDW with these conditions could compromise the statistical power of the study. To overcome this problem, we have set a narrow margin of error (1%, ie, prevalence could range between 4%‐6%) for baseline and end line estimates in each arm. Our sample size calculation also accounts for a 10% nonresponse rate per arm at both baseline and end line. To increase the effective prevalence of the APH condition, the inclusion criteria for this condition encompass APH, placenta previa, and abruptio placenta. With recent estimates in India showing an increase in prevalence of PIH to 11% [43], while moderate or severe anemia was stagnant at around 26% [39], we are confident of including sufficient RDW with these 2 conditions. Nevertheless, if the prevalence of any of the 3 HRPs falls below 4% at baseline or end line in either arm, the statistical power of the study for that HRP condition will be compromised. We acknowledge this as a limitation of the study.

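### The 1-point margin behind 1825 (rounded to 2000) women holds only up to about 5.5% prevalence, so the claim that the size suffices for commoner conditions does not follow from the formula used

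*Protocol article*

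**What the plan says.** All of this is in the protocol article, Sample Size of the Quantitative Surveys.

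- Purpose: the sample size "was determined to generate indicators for each of the 3 HRP conditions", separately for the two arms.
- Criterion: PIH prevalence of 5%, a margin of 1 point either side (4% to 6%), "with a 95% confidence level". The result is 1825 per arm and survey, rounded to 2000. The 1% margin is repeated later as set "for baseline and end line estimates in each arm".
- Principle: because the calculation uses the rarest of the three conditions, "the sample size estimated for an HRP condition with the lowest prevalence will suffice for the HRP conditions with higher prevalence as well".
- Prevalences: moderate or severe anemia 25%, later about 26%; PIH 5% to 17%, with 11% given as the recent estimate; antepartum hemorrhage (APH) alone 2% to 5%, but with the study definition widened to include placenta previa and abruptio placenta.
- Expected cases among 2000 women: 400 to 500 with anemia, 120 to 200 with APH as widened, 100 to 340 with PIH.
- Warning: power for a condition is compromised "if the prevalence of any of the 3 HRPs falls below 4% at baseline or end line in either arm".
- Rejected alternative: a 1.5-point margin with 821 women per arm, partly because about 70 to 130 women with PIH and APH per arm would be too few to compare.

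**The concern.** The one formal criterion in the section is an absolute margin on prevalence. The argument built on it, that sizing on the rarest condition covers the others, belongs to a different criterion. A reader told that the sample serves all three conditions in each arm, with a 1-point margin, will take that margin to apply to anemia and to PIH at its recent prevalence. It does not. The statement of what the design delivers is therefore wrong under its own formula. The criterion that would make the argument correct, a required number of affected women, is never set, so neither the sufficiency claim nor the 4% threshold can be checked against a target.

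**Working it through.** **Inputs**, all from the sample size section: prevalence p as listed above; margin d = 0.01; 95% confidence, z = 1.96; n = 1825 or 2000 per arm and survey. Simple random sampling is assumed, as in the protocol's own figure.

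**Step 1. Reproduce the stated figure.** n = z² p(1−p)/d² = 3.8416 × 0.05 × 0.95 / 0.0001 = 1824.8, so 1825. This matches exactly. With d = 0.015 the formula gives 811 against the stated 821, which is close enough to confirm the method.

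**Step 2. Apply the same formula at the protocol's other prevalences.** The half-width with 2000 women is z √(p(1−p)/2000).

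| Condition | p | n for ±1 point | Half-width with 2000 (points) |
|---|---|---|---|
| PIH, sizing value | 5% | 1825 | 0.96 |
| PIH, recent estimate | 11% | 3761 | 1.37 |
| PIH, upper figure | 17% | 5421 | 1.65 |
| Anemia | 25% | 7203 | 1.90 |
| Anemia, second figure | 26% | 7391 | 1.92 |

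The product p(1−p) rises up to p = 50%, so the lowest prevalence gives the smallest n.

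**Step 3. Find where ±1 point stops holding.** Solve p(1−p) = n d²/z². For n = 2000 the right side is 0.2/3.8416 = 0.0521, so p is about 5.5%. For n = 1825, p is about 5.0%.

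**Step 4. Test the lowest-prevalence argument on criteria where it could hold.**

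- Case count: 2000p gives 100 cases at 5%, 220 at 11%, 340 at 17% and 500 at 25%. The rarest condition governs, and the argument is valid.
- Relative margin: 1 point on 5% is 20% of the prevalence. Then n = 3.8416(1−p)/(0.04p), which gives 1825 at 5%, 1505 at 6%, 778 at 11%, 469 at 17% and 289 at 25%. The argument is again valid.

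**Step 5. Look for a required count.** The expected counts follow from n = 2000; they did not produce it. The 4% warning corresponds to 0.04 × 2000 = 80 cases, but no such minimum is stated. The rejected range of 70 to 130 per arm is not said to be per condition or combined. At about 5% each, 821 women yield about 41 per condition and 82 for the two together, so it may be a combined figure. If it is per condition, the plan's own lower expectation of 100 PIH cases lies inside the range called too small.

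**The case against.** The strongest reply is that the authors were thinking in case counts. They list expected numbers for each condition, reject 821 women partly because too few would be affected, and express confidence because PIH and anemia are common. The community-level primary outcome (Hypothesis and Outcomes) is a proportion among affected women, not a prevalence. The 1-point margin is illustrated only around 5%, and ±1 point is never explicitly promised for anemia. Much of this stands: on a case-count criterion the sizing principle is right. What it does not supply is the count itself. The only calculation shown is the absolute-margin one, and the sufficiency sentence is presented as following from it.

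Four stronger readings are tempting and are not supported.

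- That about 7200 women per arm are needed. This requires carrying ±1 point to 25% prevalence as a design target, which the protocol does not do.
- That anemia is the weakest condition. For outcomes among affected women it is the best supplied. At an assumed outcome of 50% under simple random sampling, 500 cases give about ±4.4 points and 100 cases about ±9.8.
- That the 4% warning is backwards. The absolute margin does become easier to meet at low prevalence, but the warning speaks of power, and fewer affected women does mean less power.
- That the sizing also fails on a relative margin because APH may be 2%. That figure is APH alone. The widened definition, with 120 to 200 expected among 2000, implies 6% to 10%, and a 20% relative margin at 6% needs only about 1505.

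**Conclusion.** The point holds as a mismatch between formula and rationale. The stated formula delivers about ±1 point only near 5% prevalence (up to about 5.5% with 2000 women). For PIH at 11% to 17% the half-width is about 1.4 to 1.65 points, and for anemia at 25% about 1.9 points, nearly twice the stated margin. The sufficiency statement does not follow from that formula. It, and the 4% warning, can be justified only by a required number of affected women or a relative margin, and the size is derived from neither.

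These figures rest on the protocol's own prevalences, 95% confidence and simple random sampling with no design effect. Applying the 1-point margin beyond 5% is a reading, supported by the sufficiency sentence and by the aim of producing indicators for every condition in each arm. The finding concerns what the design is said to deliver; it does not establish that the sample is too small for the planned comparisons.

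**What to change.** 1. State that 1825 to 2000 women give about ±1 point only at about 5% prevalence. Report the half-width for each condition at its own prevalence: PIH ±1.4 at 11% and ±1.65 at 17%, anemia ±1.9 at 25%, all before any design effect.
2. Replace the basis of the sufficiency statement with an explicit minimum number of affected women per condition, arm and survey, and give the reason for it. For example, 100 of 2000 corresponds to 5% and 80 of 2000 to 4%.
3. Express the 4% warning as that same count. A minimum of 100 would put the trigger at 5%, and a minimum of 80 at 4%, so the two statements must agree.
4. Say whether the 70 to 130 women called too few to compare is per condition or combined, and reconcile the chosen minimum with it.

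The cost is rewording of the sample size section and any matching text in the analysis plan. No additional women are needed, and the change can still be made although the baseline survey is complete. The stated precision for anemia and for PIH above about 5% becomes less favourable.

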At the community level, the primary outcome includes net change in the proportion of RDW with any of the 3 HRP conditions (anemia, PIH, and APH) whose problem was resolved prior to delivery and who reported satisfaction with the management of the condition, from baseline to end line, in intervention versus control arm. Satisfaction level of RDW is measured using a 5-point Likert scale on the topics of “attitude and behavior of staff,” “cleanliness and hygiene,” “comfort and care,” and “overall satisfaction with management of HRP condition at the facility.”

The community-level secondary outcomes include net change in proportion of RDW who received the complete ANC package during their last pregnancy*,* from baseline to end line, in intervention versus control arm. Also includes the net change in proportion of RDW who were sensitized about HRPs by ANM or MO during their last pregnancy*,* during baseline and end line, in intervention versus control arm. Other secondary outcomes include net change in the mean gestational month of first diagnosis of 3 HRPs by an ANM*,* from baseline to end line, in intervention versus control arm, and net change in the proportion of RDW diagnosed with any of the 3 HRPs who received protocol-based management or referral from an ANM*,* from baseline to end line, in intervention versus control arm. We also measure the net change in proportion of RDW diagnosed with any of the 3 HRPs, received protocol-based management or referral from MO*,* from baseline to end line in intervention versus control arm.

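### The stated 95% power is the confidence level of a one-sample precision formula; no power is derived for the primary difference-in-difference

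*Protocol article*

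**What the plan says.** Sample Size of the Quantitative Surveys starts from three inputs. The first is a prevalence: "Assuming the prevalence of PIH among RDW in the intervention arm and in the control arm, at baseline and end line surveys is 5" per cent. The second is a margin: the estimate "is not expected to differ by more or less than 1" per cent. The third is the error rate: "with a 95% confidence level". The resulting number of recently delivered women (RDW) for each arm "at baseline and at end line surveys is 1825 (rounded to 2000").

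The same section then says that, given this margin, "our study (2000 RDW per arm) is adequately powered at 95% (a conservative estimate"). Of a 1.5-point margin it says that "although the required sample size per arm will reduce to 821, the power of the study will fall below 95" per cent.

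Hypothesis and Outcomes defines the primary community outcome differently. It is the net change, intervention versus control, in the proportion of women with any of the three conditions "whose problem was resolved prior to delivery and who reported satisfaction with the management of the condition". Study Design says that quantitative indicators will be analysed by DiD.

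**The concern.** A margin of error and a confidence level describe how well one proportion is estimated. Power needs a contrast, a true difference and a type II error rate, and the section gives none of these. The quantity used for sizing (prevalence of PIH among all women) is also not the quantity on which the programme will be judged. The primary outcome is measured only in the women with a condition, and its DiD carries the sampling error of four independent cells.

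The pilot is meant to inform scale-up to all 75 districts. A null or imprecise DiD read against a claimed 95% power would look like good evidence of no effect, when moderate effects could have been missed. The risk is greater for single conditions, because the section presents the sample as large enough for each of them and speaks of condition-specific impact evaluation.

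**Working it through.** **1. The plan's own figure.** One-sample precision formula, n = z² p(1−p)/d², with z = 1.96 and p = 0.05:

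- d = 0.01: 3.8416 × 0.0475 / 0.0001 = 1824.8, so 1825. This matches.
- d = 0.015: 3.8416 × 0.0475 / 0.000225 = 811.0. The plan states 821.

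Both results use z = 1.96. Widening the margin lowers n and leaves the confidence at 95%, so nothing that could be called power falls below 95%. With 2000 women the half-width is 1.96 × √(0.0475/2000) = 0.96 points.

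**2. What 2000 per arm would give as power, even for prevalence.** In a simple two-arm comparison at two-sided 5%, 5% versus 6% has 28% power and 5% versus 4% has 33%. Power reaches 97% at 5% versus 8%.

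**3. The denominator of the primary outcome.** The section offers two routes to the number of women with a condition, per arm per survey:

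- Sum of the stated case counts, ignoring overlap: 400 + 120 + 100 = 620, up to 500 + 200 + 340 = 1040.
- Subtraction of the stated 900–1000 women without any of the three conditions: 2000 − 1000 = 1000, up to 2000 − 900 = 1100.

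These fit poorly. The summed counts leave at least 960 to 1380 women without a condition, and more if conditions overlap.

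**4. Minimum detectable DiD.** With n women in each of four independent cells, SE = √(4 p(1−p) × deff / n), and the detectable difference at 80% power is (1.960 + 0.842) × SE. The success share p and the design effect (deff) are assumptions, because the protocol gives neither. Example: n = 620, p = 0.5, deff = 1 gives SE = √(1/620) = 4.02 points, and 2.80 × 4.02 = 11.3 points.

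| Women analysed | n per arm per survey | p = 50% | p = 20% or 80% | p = 50%, deff 1.5 |
|---|---|---|---|---|
| Any condition, summed counts | 620–1040 | 11.3–8.7 | 9.0–6.9 | 13.8–10.6 |
| Any condition, by subtraction | 1000–1100 | 8.9–8.4 | 7.1–6.8 | 10.9–10.3 |
| PIH alone | 100–340 | 28.0–15.2 | 22.4–12.2 | 34.3–18.6 |

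Entries are percentage points. At 95% power, the level claimed, with p = 50% and deff = 1, they become 14.5–11.2, 11.4–10.9 and 36.0–19.5.

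**5. Power for given effects** (p = 50%, deff = 1):

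- 10-point DiD, any condition: 70% with n = 620, 89% with 1000, 91% with 1100.
- 5-point DiD, any condition: 24%, 35% and 38% respectively.
- 10-point DiD, PIH alone: 17% with n = 100, 45% with 340.

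**6. Clustering.** The plan samples 100 units per arm with about 20 women each. At an assumed intracluster correlation of 0.05, 6.2 to 11 women with a condition per unit give a design effect of 1.26 to 1.50. PIH averages only 1 to 3.4 cases per unit (1.00 to 1.12 at the same correlation), so 1.5 is a pessimistic value for PIH. Variation between the two districts in each arm is not included.

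**The case against.** The strongest defence is that the calculation was meant to produce indicators for each condition in each arm, and a precision formula is legitimate for that. Baseline data are already collected, no decision rule uses the power figure, and Data Analysis promises effect estimates with 95% confidence intervals as far as possible, which limits misreading of a null result. This stands as a defence of 2000 as a survey size. It does not rescue the power sentences, which no reading of the inputs makes true. An unseen analysis plan with a correct calculation would leave them false too.

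Some stronger readings are tempting but not supported:

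- A reader might infer that the study can detect only 9 to 11 points overall, or that it is underpowered. The protocol gives no success share and no target effect. On the favourable counts (1000–1100), a 10-point DiD has about 90% power at a 50% share under simple random sampling. What can be said is that power is not established.
- A reader might take the 18,000 high-risk pregnancies among 60,000 as the denominator. That is a programme-wide count of high-risk pregnancies, not the share with the three surveyed conditions.
- A reader might scale effects down by the full 30%–44% using private or NGO care. The upper part includes mixed users, whom the programme is expected to reach partly, and the shares refer to antenatal care users in general.
- A reader might call the 70–130 women expected at the wider margin wrong. The figure is approximate and can be read as PIH and antepartum hemorrhage combined; at about 5% each, 821 women give about 82.
- The gap between 821 and 811 is a slip of 1.2% in a rejected alternative and carries no weight on its own.

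PIH alone is not the primary outcome, so its weak precision limits condition-specific results and is not a failure of the primary analysis.

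**Conclusion.** The point stands. The 95% is a confidence level, and the statements that the study is powered at 95% and would lose power at a wider margin are wrong as written. This follows from the protocol's own inputs and needs no assumption. It is equally firm that no power is derived for the primary community DiD.

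The size of the consequence is conditional. At 80% power, two-sided 5% and simple random sampling, the minimum detectable DiD for any condition runs from about 6.8 to 11.3 points across both sets of counts and success shares of 20% to 80%. For PIH alone it runs from about 12 to 28 points. An assumed design effect of 1.5 at a 50% share raises these to about 10.3–13.8 and 18.6–34.3. These are illustrations and not properties of the study, because the success share, the clustering and the true number of women with a condition must come from the baseline.

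**What to change.** In Sample Size of the Quantitative Surveys:

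- Delete the claim of 95% power and the clause saying that power falls below 95% at a wider margin.
- State instead that 2000 women per arm per survey give a 95% confidence interval of about ±1 point on a 5% prevalence under simple random sampling.
- If the comparison with a 1.5-point margin is kept, give 811 in place of 821.
- From the completed baseline (observed number of women with a condition, success share, intracluster correlation), state the minimum detectable DiD for the primary community outcome at 80% power, and report the corresponding precision for single-condition DiDs.
- Reconcile the expected case counts (620 to 1040 in total) with the stated 900–1000 women without any of the three conditions.

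The cost is wording and one calculation on data already in hand. The published figure becomes less favourable, and no extra participants are needed.

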### Survey Design

A multistage sampling approach will be used to select RDW from each arm. As census data at the village and ward level is old (2011), the accredited social health activist (ASHA) jurisdiction will be used to serve as a primary sampling unit (PSU). A total of 50 PSUs per district (100 per arm) will be selected using a 2-stage sampling approach. During baseline, the 2023 list of RDW in an ASHA’s jurisdiction served as the basis for the selection of a PSU. Assuming an average PSU will have 20 RDW, we expect to cover 1000 RDW per district (2000 per am) at baseline and end line surveys.

As part of the first stage of sampling, 50 PSUs in each district were allocated according to the proportion of the block population of the district. As part of the second stage of sampling approach, the allocated number of PSUs in a block was selected using the probability proportionate to size sampling technique.

During the baseline, in a selected PSU, the list of women who were delivered in the past 1 year, regardless of delivery outcome, and the delivery data maintained by ASHA and anganwadi workers (AWWs) served as the basis for identifying the eligible respondents for survey. This list by ASHA and AWWs was cross-verified with the list available with the ANM of the respective PSU, and a comprehensive list of RDW to be approached for interview was prepared. By adopting this strategy, we eliminated the need for doing households listing exercise to identify eligible RDW in the selected PSUs.

In a sampled PSU, all the households with eligible respondents (RDW) were approached by female investigator or supervisor for consent or assent for a face-to-face interview (Multimedia Appendix 7). All consented RDW participants were interviewed by female investigators, mostly in RDW’s home. To ensure 100% enumeration of eligible respondents in a PSU, a “snowballing” technique was also used with interviewed RDW to check if any peer RDW in her neighborhood was missed by the ASHA, AWW, or ANM list. If any new RDW is found through the snowballing technique, she was interviewed, provided she belongs to the selected PSU. Table 4 provides the inclusion and exclusion criteria used for selecting the respondents for the baseline and end line surveys in the 4 study districts of UP.

**Table 4. T4:** Inclusion exclusion criteria for respondents of baseline and end line surveys.

Respondent	Data collection method	Inclusion criteria	Exclusion criteria
RDW^a^	Personal interview	Woman aged 15‐49 years, have had delivery during the past 1 year from the date of survey Details of such woman are available with ASHA^b^, AWW^c^, and ANM^d^ in the sampled PSU^e^ or woman was identified through snowballing technique from an interviewed RDW RDW who is resident of nonsampled PSU but had delivery in sampled PSU in past 1 year and is willing to participate in survey	All those who do not give consent to participate in the survey RDW listed by ASHA, AWW, and ANM, but not available for interview on days of survey Had delivery just within 3 days of survey Maternal deaths and RDWs with severe illness and unable to participate in interview
District officials and Specialist gynecologists	IDI	Currently serving in the stated position in the survey district	With less than 1 year of experience in the current position, in the survey district Who do not give consent to participate in the survey
Medical officer and ANM	SSI	Currently serving in the stated position in the sampled PHC^f^ and HSC^g^	With less than 1 year of experience in the current position in sampled PHC and HSC Who do not give consent to participate

a RDW: recently delivered women.

b ASHA: accredited social health activist.

c AWW: anganwadi worker.

d ANM: auxiliary nurse midwife.

e PSU: primary sampling unit.

f PHC: primary health center.

g HSC: health subcenter.

Using the above-stated survey design, tools, and inclusion and exclusion criteria, data for the baseline survey component of the impact evaluation of the IHRPTM program were collected during June-October 2024. Baseline qualitative data from system stakeholders were collected by ARMMAN researchers from 4 districts during June-August 2024. Baseline quantitative data were collected from >4000 RDW by around 75 female investigators and supervisors, during September-October 2024, from 200 PSUs, spread across 4 districts and 2 arms.

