While designing the impact evaluation of the UP pilot, the following contextual variations in the scale of direct beneficiaries were considered. The program engaged ANMs (>400 in UP vs >9000 in Telangana and >15,000 in AP), MOs (>100 in UP vs >1000 in Telangana and >1800 in AP), and specialists (>10 in UP vs >400 in Telangana and >500 in AP). Indirect beneficiaries also varied substantially, with approximately 60,000 pregnancies per year in UP compared with 700,000 in Telangana and 900,000 in AP, translating to roughly 18,000 HRPs per year in UP versus 200,000 in Telangana and 300,000 in AP. Training timelines also differed, while training all ANMs on 6 phase-1 protocols required approximately 1 year in Telangana and 9 months in AP, >400 ANMs in UP were trained in just a few days. Moreover, digital interventions were introduced within 2-3 months of program initiation in UP, compared with more than 3 years in Telangana and 1 year in AP, as these digital interventions were still evolving when implementation began in Telangana.

Thus, considering UP’s comparative advantage over Telangana and AP, sufficient number of direct and indirect beneficiaries, the rapid introduction of all interventions in quick succession, and additional scope for keeping a control arm, the UP impact evaluation design is expected to provide generalizable evidence on the program’s impact, even with its shorter duration (18 months) and smaller scale (2 intervention districts and 3 HRP protocols). In UP, the impact evaluation will be confined to the following 3 HRP conditions: anemia (moderate and severe), PIH, and APH.

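### The 2000 women per arm come from a simple-random-sampling formula with no design effect, so the stated 1-point margin is not supported, and 2 districts per arm cannot carry the causal and generalisable claims

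*Protocol article*

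**What the plan says.** All references are to the protocol article.

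- **Sample Size of the Quantitative Surveys.** Pregnancy-induced hypertension (PIH) prevalence in both arms "at baseline and end line surveys is 5" percent. The estimate "is not expected to differ by more or less than 1" percentage point, "with a 95% confidence level". The number of recently delivered women needed per arm "at baseline and at end line surveys is 1825 (rounded to 2000").
- **Same section, on nonparticipation.** The authors say that "we have set a narrow margin of error (1%, ie, prevalence could range between 4" and 6 percent). They add that the calculation also covers 10% nonresponse, and they describe 2000 per arm as conservative. No ICC or design effect appears.
- **Survey Design.** "A total of 50 PSUs per district (100 per arm) will be selected using a 2-stage sampling approach". A primary sampling unit (PSU) is one community health worker's (ASHA's) area, drawn with probability proportionate to size and assumed to hold 20 eligible women on average. "In a sampled PSU, all the households with eligible respondents (RDW) were approached by female investigator or supervisor".
- **Study Geography and Data Analysis.** The programme is allocated by district, 2 against 2. The difference-in-difference (DiD) model is described by arm, survey round and interaction terms. The descriptive DiD is said to give the programme's causal effect. No variance estimator or weighting is named.
- **Rationale for the Study, Overview.** "the UP impact evaluation design is expected to provide generalizable evidence on the" programme's impact.

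**The concern.** Women in one ASHA area live close together and are likely to share frontline providers. Textbox 1 gives one ASHA per 1000 population and one auxiliary nurse midwife (ANM) per 5000. Several outcomes depend directly on those providers, such as being sensitised about high-risk pregnancy or receiving protocol-based management. Some correlation within areas is therefore to be expected, and 20 women from one area carry less information than 20 independent women. A sample size that ignores this overstates precision.

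A second level lies above the PSUs. The programme varies only between districts. The Discussion itself expects official transfers and departures of medical officers. Any such change that differs between districts over the 18 months enters the DiD exactly as a programme effect would. The results are meant to inform scale-up across 75 districts, so the stated strength of the evidence matters.

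**Working it through.** **Inputs from the article:** p = 0.05, margin d = 0.01, 95% confidence (z = 1.96), 100 PSUs per arm, m = 20 women per PSU, 10% nonresponse. **Assumed, because the article gives no figure:** ICC of 0.005 to 0.05, and the standard deviation (SD) of district-specific change.

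**1. The plan's figure.** n = z²p(1−p)/d² = 1.96² × 0.05 × 0.95 / 0.01² = 1824.8, hence 1825. This is the simple-random-sampling formula, with a design effect of 1. At d = 0.015 it gives 811, close to the 821 the article quotes for that margin.

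**2. Room left by rounding.** 2000/1825 = 1.096. Setting 1 + (20−1) × ICC = 1.096 gives ICC ≈ 0.005.

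**3. Nonresponse.** 1825/0.9 = 2028, which already exceeds 2000. If 2000 are approached and 1800 respond, the margin is 1.96 × √(0.0475/1800) = 1.007 points, even with no clustering.

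**4. Margin with clustering, 2000 completed interviews.** Design effect = 1 + 19 × ICC; margin = 1.96 × √(0.0475 × design effect / 2000); effective n = 2000 / design effect; n needed = 1825 × design effect, then divided by 0.9.

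| ICC (assumed) | Design effect | Margin (points) | Effective n | n for ±1 point, completed | Allowing for nonresponse |
|---|---|---|---|---|---|
| 0.005 | 1.095 | 1.00 | 1826 | 1999 | 2221 |
| 0.01 | 1.19 | 1.04 | 1681 | 2172 | 2413 |
| 0.02 | 1.38 | 1.12 | 1449 | 2519 | 2798 |
| 0.05 | 1.95 | 1.33 | 1026 | 3559 | 3954 |

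Unequal PSU sizes make this slightly worse: with a coefficient of variation of 0.3, the margins at ICC 0.01 to 0.05 are 1.05 to 1.36. Allocating PSUs by block may offset a little.

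**5. Women with a high-risk condition.** The article expects 400–500 with anaemia, 120–200 with antepartum haemorrhage and 100–340 with PIH per arm. Summed without overlap this is 620–1040. Taking 2000 minus the 900–1000 unaffected gives 1000–1100. That is roughly 6 to 11 women per PSU. At ICC 0.02 the design effect is 1 + 5.2 × 0.02 = 1.10 to 1 + 10 × 0.02 = 1.20, so standard errors grow by about 5% to 10%. For PIH alone (1 to 3.4 cases per PSU) the design effect is 1.00 to 1.12, even at ICC 0.05.

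**6. District level (illustration).** Let each district-by-survey deviation have SD τ. Each district's change has variance 2τ², the mean of two districts τ², and the difference between arms 2τ². For τ = 2 points this adds √2 × 2 = 2.8 points of standard error. The sampling standard error of the DiD with 1000 women per arm and survey at p = 0.5 is √(4 × 0.25/1000) = 3.2 points. A nominal 5% test that ignores τ then has a true type I error of about 7%, 14% or 24% for τ = 1, 2 or 3 points. A district-level analysis has about 2 degrees of freedom, with a critical value of 4.30.

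**The case against.** **The analysis is not shown to be wrong.** A reader might infer that the DiD confidence intervals will be too narrow, or that the survey will be analysed unweighted. The documents do not support either. Data Analysis names model terms but no variance estimator or weights, Study Design says the analysis plan will be locked, and such detail is commonly left to a statistical analysis plan. Only the conditional holds: intervals would be too narrow if clustering were ignored.

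**The 1-point margin is not shown to fail.** With 2000 completed interviews it fails only if the ICC exceeds about 0.005, and the article gives no ICC. At 0.01 to 0.02 the miss is modest. The nonresponse shortfall is also small in itself, and baseline produced more than 4000 interviews over both arms. This stands, but it does not rescue the claim that the figure is conservative: a figure with no allowance for clustering and too little for nonresponse is not.

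**The margin concerns PIH prevalence, not the primary outcome.** This is correct. The factor 1 + 19 × ICC applies to full-sample indicators and should not be carried over to the high-risk subgroups, where step 5 applies.

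**Shared care is incomplete.** The article does not say that women in a PSU use the same facility. It reports that about 30% of antenatal care in the state is exclusively private or non-governmental. This argues for a lower ICC, not for zero.

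**The 2-versus-2 design was given.** The government chose the intervention districts for a pilot. The article acknowledges nonrandom allocation and plans matching and covariate adjustment. That is fair as to design, but adjustment for women's characteristics does not remove district-specific change over time, and the stated limitations do not mention it.

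**Conclusion.** The point holds for the sample size statement and for the strength of the claims. The 1825 assumes independent women, while the survey takes all eligible women in 100 areas per arm. The rounding to 2000 is used up by an ICC of about 0.005 or by the nonresponse allowance, and cannot cover both. Over an assumed ICC of 0.01 to 0.05 the full-sample margin is 1.04 to 1.33 points, a modest to moderate loss, and less in the high-risk subgroups. The conservative label is not supported.

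The district problem does not depend on the ICC. With 2 districts per arm, district-by-time change is inseparable from the programme, and PSU-clustered standard errors do not cure this. How large it is depends on τ, which is unknown, so the type I error figures are illustrations only. The causal and generalisable wording goes further than this design allows.

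**What to change.** 1. Estimate the ICC from the baseline survey (over 4000 women, 200 PSUs) for PIH prevalence and the main full-sample indicators. Restate the margin with the resulting design effect and an explicit nonresponse allowance, and drop the conservative label.
2. State that the women's survey will be analysed with PSU-clustered standard errors and sampling weights. Weights are needed because probability-proportionate-to-size selection followed by full enumeration gives women in larger areas a higher chance of inclusion. If an analysis plan already says so, refer to it.
3. Report the DiD for Shravasti–Gonda and Sambhal–Budaun beside the pooled estimate. This is descriptive: two pairs agree in direction half the time under no effect, so agreement should not serve as a test.
4. State as a limitation that district-specific change over time cannot be separated from the programme with 2 districts per arm, even with clustered standard errors. Limit the causal and generalisable wording to match.

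The cost is wider stated margins and more modest claims. No extra participants are needed, and the changes can be made before the end line analysis planned for March–June 2026. Revisiting the same PSUs or adding PSU fixed effects is optional.
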